## 10 ETHICAL ASPECTS

### 10.1 Declaration of Helsinki / Good Clinical Practise (GCP)

The study will be performed according to the Declaration of Helsinki from 1996. That is the World Medical Association Recommendations guiding physicians in biomedical research involving human subjects (which was adopted by the 18th World Medical Assembly at Helsinki in 1964 (amended at subsequent meetings at Tokyo in 1975, Venice in 1983, Hongkong in 1989 and 1996 (Art. 3, Abs. 2 Guideline 2005/28/EG)).

Additionally it is the responsibility of all engaged in research on human beings to ensure that the study is performed in accordance with the international GCP standards and according to all local laws and regulations concerning clinical studies.

GCP requires that the clinical protocol, any protocol amendments, the Investigator's Brochure, the informed consent and all other forms of subject information related to the study or any other necessary documents be reviewed by and IEC/IRB. The IEC/IRB will review the ethical, scientific, and medical appropriateness of the study before it is conducted. IEC/IRB approval of the protocol, informed consent and subject information and/or advertising, as relevant, will be obtained prior to the authorization of drug shipment to a study site.

In this study no Investigator's Brochure will be submitted, because both study drugs are approved and marketed in the indication ankylosing spondylitis in adults (according to Art. 11 REGULATION (EU) No 536/2014). Instead, the German version of the "Summary of product characteristics" ("Fachinformation") is provided.

### 10.2 Patient Information and Informed Consent

The investigator will explain the nature of the study to the subject, and will answer all questions regarding this study. It is the responsibility of the investigator to obtain written informed consent from each subject participating in this study, after adequate explanation of aim, importance, anticipated benefits, and potential hazards and consequences of the study according to § 40 Abs 2 and § 40 Abs. 2a of the German drug law (AMG). Written informed consent must be obtained before any study specific procedures are performed, according to §40 Abs. 1 S. 3 Nr 3 b) and c) AMG. It must be also explained to the subject that they are completely free to refuse to enter the study or to withdraw from it at any time for any reason without incurring any penalty or withholding of treatment on the part of the investigator.

By signing the consent form, the subject/patient agrees with the "unwiderrufliche datenschutzrechtliche Einwilligung" according to § 40 Abs. 2a AMG. The subject/patient also agrees to allow the monitor/auditor/health authorities to verify the collected patient data against the subject's/patient's original medical records for the purpose of source data verification.

A copy of the informed consent form will be given to the subject and the original will be placed in the subject's medical record. An entry must also be made in the subject's dated source documents to confirm that informed consent was obtained prior to any study-related procedures and that the subject received a signed copy.

If new safety information results in significant changes of the risk/benefit assessment, the consent form should be reviewed and updated if necessary. All subjects (including those already being treated) should be informed of the new information and must give their written informed consent to continue in the study.

If the general practitioner is informed of his patients' participation in the clinical study, this should be mentioned in the consent form.

### **10.3 Insurance coverage**

The insurance coverage (study subject insurance) laid down in § 40 AMG is in force. For each subject, the Sponsor has taken out insurance.

## 11 INDEPENDENT ETHICS COMMITTEE AND REGULATORY AUTHORITIES

### 11.1 Approval of the Study by Regulatory Authorities and Independent Ethics Committees

According to §§ 40-42 of the AMG it is the responsibility of the Sponsor to obtain and maintain independent approval from the federal regulatory authority (BfArM/PEI) and a positive opinion from the competent ethics committees to conduct the study.

The written approval of the Central Independent Ethics Committee of the „Landesamt für Gesundheit und Soziales, Ethik-Kommission des Landes Berlin“ will be obtained prior to the enrolment of patients.

Furthermore, the commencement of the study together with the study protocol and the decision of the Central Ethics Committee involved will be reported to the PEI (Paul-Ehrlich-Institut, Langen, Germany) and the locally responsible Ethics Committees and local supervisory authorities.

### 11.2 Notification of the Study

According to § 67 German drug law (AMG) the sponsor or the sponsor's designee is responsible to notify competent regional authority and the federal regulatory authority about the study and all principal investigators of the participating investigational sites. If no other agreements are made, the sponsor or the sponsor's designee will take over responsibility for investigator's obligation to report (§ 12 (3) GCP-V).

### 11.3 Report and Documentation Obligation

The sponsor or the sponsor's designee is responsible to comply with the report and documentation obligation according to § 13 GCP-V.

The investigator is responsible to comply with the report and documentation obligation according to § 12 GCP-V.

## 12 CONDITIONS FOR MODIFYING THE PROTOCOL

Protocol modifications to on-going studies must be made via protocol amendment. The sponsor is responsible to obtain independent approval for the amendment from the federal regulatory authority (PEI) and a positive opinion from the competent ethics committees if required according to § 10 GCP-V.

According to § 67 AMG amendments competent regional authorities and the federal regulatory authority must be notified about the amendment, if they concern items according to § 12 Abs. 1 GCP-V.

### 13 STATISTICAL ANALYSIS PLAN

The study consists of a 12-week run-in period, 96-week core period (randomized treatment) and 4-week follow-up period. The primary efficacy endpoint will be the absolute progression of the mSASSS score over two years of therapy in both treatment groups. The primary analysis will be based on the mean of the mSASSS scores evaluated by 2 trained readers for the spinal x-rays performed at screening and at Week 108 in the ITT population.

A database lock will occur for the purposes of the efficacy and safety analysis, once all data up to week 112 have been collected and cleaned.

Study biostatistician: [name], German Rheumatism Research Center (Deutsches Rheumaforschungszentrum – DRFZ, Berlin).

#### 13.1 Definition of Population for Analysis

Primary analysis will be based on the ITT population. A secondary analysis will be based on all patients with complete sets of radiographs. For the purpose of safety analyses all patients receiving at least one dose of study drug (starting at Visit 2) will be included.

#### 13.2 Intent-to-Treat Population

Intent-to-treat population (ITT) is defined to include all subjects who received at least one dose of study medication in phase II of the study (starting from Visit 6) and where the primary variable was measured at least once under study medication.

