|                 | 
n=190; assuming a 10% screening failure rate approximately.
 
To be allocated to trial:
n=170 patients with active AS despite treatment with NSAIDs alone will be included in the phase I of the trial and treated with Golimumab. Only patients with good clinical response after 12 weeks of treatment will be enrolled in the phase II of the trial. It is assumed that approximately 60% (n=100) of patients included in phase I will continue in the phase II of the study, considering that elevated CRP at baseline is currently the best response predictor for TNF-blocker therapy.
 
To be analysed:
n=100 (n=50 in each group) patients will enter phase II of the trial (intention-to-treat population - ITT) after 1:1 randomization.
 
Statistical analysis:
 
Efficacy:
Efficacy of the therapy in reduction of radiographic spinal progression will be assessed by the modified Stoke Ankylosing Spondylitis Spine Score (mSASSS). mSASSS is a radiographic score measuring structural changes in the lumbar and cervical spine. Images will be scored by 2 trained readers in a blinded manner that allows the open-label (although randomized) design of the trial.
The primary efficacy endpoint will be radiographic spinal progression assessed by the change in the mSASSS score over two years of therapy in both groups. The primary analysis will be based on the intention-to-treat population, a secondary one in patients with complete sets of radiographs at two time points. A two-sided Mann-Whitney U-test will be applied to compare the mSASSS progression between both treatment groups in both analyses.
 
Safety:
Safety outcome will include absolute number and percentage of patients who experienced adverse events (AE), serious AE, AE of interest (infections, malignancies, gastrointestinal events: ulceration, bleeding, perforation, gastric outlet obstruction; thrombotic cardiovascular events: myocardial infarction, stroke, pulmonary artery embolism, peripheral arterial of venous thrombosis; renal and hepatic function deterioration), as well as a proportion of patients who discontinued the study because of AEs.
In order to address possible long-term safety issues related to long term use of NSAIDs a safety Follow-Up Visit will be performed 3 months after discontinuation of the study treatment (either week 108 or the last study visit in the case of early discontinuation).
Safety population will include each patient who received at least one dose of Golimumab with or without Celecoxib. Statistical comparisons will be based on event rates per 100 patient years of exposure. Rates will be compared by exact Poisson methods.
 
Secondary endpoint(s):
Mann-Whitney U-test, linear mixed models, and Chi-square test will be used in order to evaluate differences in the secondary outcome parameters between treatment groups.
 |

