### *X-rays of the spine*

X-rays of the lumbar and cervical spine (lateral views) will be performed during screening only if there were no image performed within the previous 24 months. Those images are central for the conduct of the study (primary outcome; inclusion criterion #5b and exclusion criterion #10). Quality of the x-rays should allow this assessment, i.e., images should be available in electronic form or as x-ray film (no paper printouts). If no images fulfilling these criteria are available, X-rays of the cervical and lumbar spine should be performed during the screening period. A second set of X-rays of lateral cervical and lumbar spine must be performed at Week 108, or in case of an early termination (ET) if the patient reached at least Week 84..

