### 13.5 Efficacy analyses

The primary analysis will be based on all patients who entered phase II of the trial (ITT population). Multiple imputation methods with mSASSS score at baseline as covariate (SAS procedure PROC MI) will be applied to deal with missing radiographs in the primary analysis. The Mann-Whitney test will be used to compare the primary outcome (change in the mSASSS score) between the treatment groups. Cumulative probability plots of will be built to visualise the finding.

In a secondary analysis the Mann-Whitney test will be used to compare radiographic progression in the subgroup of patients with complete sets of radiographs. A likelihood approach will be applied to deal with missing data in secondary outcome parameters assessed at multiple time points (Molenberghs G., Kenward M.G. Missing data in clinical studies. Chichester: John Wiley & Sons; 2007). For that reason linear mixed models (SAS procedure PROC MIXED) will be applied to compare means of secondary outcome parameters over time. Time and group, (time\*group) will be included in these models as fixed effects and patient-ID as a random parameter (included in PROC MIXED via the repeated statement with type = un for an unstructured covariance matrix). In the case of skewed data PROC MIXED will be applied to log-transformed parameter (CRP) or non-parametric tests (Mann-Whitney test, non-parametric analysis of covariance) will be applied (e.g., for biomarker data). Spearman rank correlation and non-parametric analysis of covariance will furthermore be used to investigate the association between radiographic progression and biomarkers of inflammation and bone/cartilage turnover (Bathke A, Brunner E. A nonparametric alternative to analysis of covariance. In: Akritas MG, Politis DN eds. Recent advantages and trends in nonparametric statistics. Amsterdam: Elsevier Science and Technology 2003: 109-20).

Nonresponder imputation for missing response data and chi-square tests will additionally be applied to compare response rates. Two-sided p values < 0.05 will be considered to be statistically significant.

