### 13.8 Sample Size and Power Calculation

The study is designed for a total sample size of  $n = 170$  subjects who will enrol in the phase I of the study. The power calculations are based on the findings of Kroon et al, our own results from GESPIC Cohort, and those of Braun et al. We assume a worsening in the mSASSS score of  $1.7 \pm 2.8$  in patients of the control group and of  $0.2 \pm 1.6$  in patients with continuous NSAIDs intake. We considered such a difference of 1.5 mSASSS units as clinically relevant and planned the sample size of this study by means of a two-sided ( $\alpha = 0.05$ ) Welch-Satterthwaite t-test accordingly. A smaller treatment effect, which was

observed in a trial comparing diclofenac continuously vs. on demand and which would be missed by our trial design, would be considered as clinically not relevant. To detect the difference with an 80% power, the sample size of  $n = 38$  in each group is needed in the phase II of the trial. This is also true if the Mann-Whitney test is applied. Since in the case of skewed non-normal distributions (like the mSASSS) the power of the Mann-Whitney-test is not lower than that of the t-test even in the case of ties (Rasch D et al, 2007). However, the power will decrease by the application of multiple imputations to deal with missing radiographs of dropouts in the ITT population. We estimated this decrease by: a) an estimation of dropout rates and b) the use of own mSASSS data. Considering that all subjects enrolled in the phase II will be responders to Golimumab therapy receiving this same treatment for the whole period of the trial, along with our experience in conducting randomized controlled trials, we presume dropout rates of less than 20% during phase II. For this reason and based on our own mSASSS data, we expect an increase in the variance of mSASSS progression because of multiple imputation by less than 25%. Considering this possible increase, a sample size of  $n = 100$  patients is needed for phase II of the trial to detect the expected and clinically relevant difference of an average 1.5 mSASSS points with an 80% power in the ITT population. In addition we assumed that 60% of the subjects enrolled in phase I of the study ( $n = 100$  out of 170) would be eligible for randomization and participation in phase II (based on the rate of the BASDAI response of at least 2 absolute points in AS patients with elevated CRP).

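### Section 13.2 admits to the ITT population only patients who have the follow-up spine film, which removes the dropouts whose films the primary analysis is meant to impute

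*Protocol*

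**What the plan says.** The protocol defines the primary analysis population in two ways.

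- **Section 13.2** requires at least one phase II dose and adds a measurement condition: "and where the primary variable was measured at least once under study medication".
- **Section 13.5** has no such condition: "The primary analysis will be based on all patients who entered phase II of the trial (ITT population)". It then specifies multiple imputation, with baseline mSASSS as covariate, which "will be applied to deal with missing radiographs in the primary analysis".
- **Synopsis, statistical considerations:** "n=100 (n=50 in each group) patients will enter phase II of the trial (intention-to-treat population - ITT) after 1:1 randomization".
- **Section 13.8** allows for a loss of power through the "application of multiple imputations to deal with missing radiographs of dropouts in the ITT population".
- **Section 13.7, item 3** relies on the methods of 13.5 to deal with bias from patients who lack a follow-up film.
- **Section 13.1** lists a separate secondary analysis: "A secondary analysis will be based on all patients with complete sets of radiographs".

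The filming schedule (section 3, footnote o, and section 6.7) has two time points. The first film is taken at screening, or is an existing film up to 24 months older. The second is taken at Week 108, "or in case of an early termination (ET) if the patient reached at least Week 84". There is no interim film.

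**The concern.** The first film always precedes study medication, so the measurement condition in 13.2 can be met only by the second film. A patient who leaves before Week 84 gets no second film and so drops out of the ITT population. These are the dropouts for whom 13.5 and 13.8 plan imputation.

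Entry to the primary analysis would then depend on an event after randomisation: staying in an open-label trial long enough to be filmed. That event can differ by arm. Only the combination arm takes celecoxib, and section 6.6.1 withdraws combination patients whose celecoxib is interrupted for more than 4 weeks; the control arm has no counterpart to that rule. The safeguard claimed in 13.7, item 3, would not operate.

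Two statisticians, one following 13.2 and the other 13.5, would analyse different patients for the primary endpoint. If this stays open, the choice could be made after the outcomes are known.

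**Working it through.** **Step 1. Which patients satisfy 13.2?**

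- Baseline film: at screening or earlier, so never under study medication.
- Follow-up film: Week 108, or early termination from Week 84.
- Result: the patients with an on-treatment measurement are those with a follow-up film.

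**Step 2. Compare the two readings.**

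| | 13.2 as written | 13.5, 13.8, synopsis |
|---|---|---|
| Primary set | dosed in phase II, with follow-up film | all entering phase II (100) |
| Follow-up films to impute | essentially none | all missing ones |
| Secondary both-films analysis | nearly the same set as the primary | a real comparison |

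**Step 3. How many patients are affected?** Section 13.8 presumes phase II dropout below 20%, so 20% is a ceiling.

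- Upper bound, if every dropout goes unfilmed: 0.20 × 100 = 20 patients.
- If dropout is even over the randomised period (an assumption, not in the protocol): that period is 108 − 12 = 96 weeks, and Week 84 falls 84 − 12 = 72 weeks into it. The share leaving before Week 84 is 72/96 = 75%, so 0.75 × 20 = 15 of 100 could never qualify.

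**Step 4. Sample size and power.** Inputs from 13.8: difference 1.7 − 0.2 = 1.5, SDs 2.8 and 1.6, two-sided alpha 0.05, Welch-Satterthwaite t-test. With n per arm and variance inflation f, SE = √[f(2.8² + 1.6²)/n], and power comes from the noncentral t distribution with noncentrality 1.5/SE.

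- The protocol's own figure: n = 38, f = 1 gives SE = √(10.40/38) = 0.523 and power 80.5%; n = 37 gives 79.4%. The stated 38 per group is reproduced.
- With the protocol's ceiling of 25% more variance from imputation (f = 1.25), 47 per arm are needed (80.4%), and the planned 50 give 82.8%.
- 13.2 read literally at 20% loss, no imputation: 40 per arm, f = 1, power 82.5%. At 10% loss: 45 per arm, 86.8%.

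Power hardly depends on the reading. What changes is who is analysed.

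**Step 5. Illustration of the selection effect (assumed, not protocol figures).** Suppose a share q of the combination arm leaves before Week 84 and progresses like control, while control dropouts progress like other controls. The film-only difference stays at 1.5. The all-randomised difference is 1.7 − [(1 − q) × 0.2 + q × 1.7] = 1.5(1 − q):

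- q = 10%: 1.35
- q = 20%: 1.20
- q = 30%: 1.05

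**The case against.** The strongest reply is that the intended analysis is clear. Section 13.5 is the operative efficacy section, the synopsis, 13.7 and 13.8 agree with it, and 13.2 looks like a standard definition carried over unadapted. On that view this is a one-clause inconsistency with adequate power either way. The description of intent is fair. But 13.2 is the section that formally defines the population, and the per-protocol set is built on it, so the conflict has to be resolved in the text.

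Several points of degree stand:

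- The 13.2 set is not strictly study completers, because patients stopping from Week 84 onward can be filmed.
- A partial or unreadable film could still leave something to impute, so almost nothing is more exact than nothing.
- The 20% is a ceiling, and the even-dropout pattern is an assumption.
- The patients added above 38 per arm would not be wasted under 13.2; they would offset attrition.

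The reply also notes that imputation would not by itself remove the bias. The only covariate named is baseline mSASSS. If imputation is done within arm, dropouts are made to resemble filmed patients of the same arm and baseline, so it would not recover the values in step 5. That is correct: restoring the full randomised set is necessary for the protection the protocol claims, but it is not a guarantee.

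Finally, the one-dose condition in 13.2 probably excludes few or no patients, since golimumab is scheduled for both arms at the Week 12 visit. The measurement condition is what does the damage.

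**Conclusion.** The concern holds for 13.2 as written. The definition contradicts 13.5, 13.8 and the synopsis, turns the primary analysis into one of patients with a follow-up film, and makes the secondary both-films analysis nearly a repeat of it. Up to 20 of 100 randomised patients would be excluded at the protocol's dropout ceiling, about 15 of them unavoidably if dropout is even over the 96 weeks.

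The consequence is possible bias and an undetermined primary population; power is not lost. The size of any bias cannot be derived from the protocol, because it gives no arm-specific dropout and no progression figures for dropouts. The point must be settled because it decides who enters the primary comparison.

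**What to change.** Rewrite 13.2 so that the ITT population is all patients randomised at Week 12, analysed in the arm assigned, with no condition on dosing or on having an on-treatment film. Removing the measurement condition is the essential part; dropping the dose condition brings 13.2 fully into line with 13.5 and the synopsis. Use this set, with the planned multiple imputation, for the primary analysis, and keep patients with both films as the secondary set.

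The cost is one sentence, by amendment or in the SAP, fixed before database lock. It needs no new data and no change to the sample size.

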#### 13.3 Per Protocol Population

Per protocol population is defined as a subset of the ITT population who completed the study without any major protocol violations. Specific reasons for warranting exclusion will be agreed and documented in a statistical analysis plan prior to the closing of the database. Not all protocol deviators and violators will be excluded from the per protocol population.

#### 13.4 Safety Population

The safety population is defined to include all subjects who received at least one dose of the trial medication, whether withdrawn prematurely or not.

